##### Photography sub-study

To give the widest range of angles possible, we will recruit sufficient participants to provide 100 photograph sets before surgery and will also collect as many photograph sets as possible at 3 months, 6 months, 1 year, and 2 years post-treatment.

Participants who consent to participate in the photography sub-study will be shown how to take the required photographs of their hand at baseline and will be provided with detailed instructions. This will include a template to aid placement of the participant’s hand, an information leaflet on how to submit photos, and a link to a video showing how to take photographs. Documentation will be reviewed and approved by the patient and public involvement group prior to use in the study.

Sub-study participants will be asked to take standardised photographs of their study reference hand at baseline and all subsequent time points. Participants will receive a text message or letter at each time point to remind them to return photographs to the study team for this sub-study via email, SMS or post.

##### Nested retention studies within a trial (SWAT)

We will undertake two nested randomised controlled trials. One will evaluate the effectiveness of a thank you card on participant retention; the other the effectiveness of a festive greetings card on participant retention. The inclusion of these SWATs was not planned at the outset of the trial, and therefore, due to the timing of identification and implementation (thank you cards decision December 2018, decision July 2019, implementation May 2019; festive greetings card implemented December 2019), it will not be possible to utilise a factorial design and so each will be handled as a separate SWAT.

In the first SWAT, participants will be allocated to either receive a thank you card at 9 months post-randomisation or to not receive a thank you card. In the second SWAT, participants will be allocated to receive a festive greetings card or to not receive a card.

All participants randomised into the main DISC Trial and who remain as fully participating (i.e. have not fully withdrawn, withdrawn from postal follow-up or have died) will be eligible and randomised for each of the two SWATs. The exception will be DISC participants due to receive a thank you card in December 2019 who will be excluded from the festive greeting card SWAT.

The primary outcome of both embedded trials will be the difference in retention rate between those who receive the card, and those who do not. The cost per participant retained will serve as a secondary outcome for both SWATs. The thank you card SWAT will also assess the completeness of outcome data, and the Christmas card SWAT will assess time since intervention and response rate.

#### Participant timeline {13} (Fig. 1)

##### Sample size {14}

Previous survey data (880 patients) showed the standard deviation of the scores for the 11 items in part 2 of the primary outcome (PEM) at baseline to be 22 points (unpublished). We estimate that a six-point difference on the PEM at 12 months is the threshold at which treatment differences become important and represents an appropriate non-inferiority margin.

**Fig. 1 Fig1:**
[figure not shown]
Participant flow diagram

An effective sample size of 568 participants (284 per arm) is required to obtain 90% power to assess non-inferiority of collagenase based on the upper limit of a two-sided 95% confidence interval (equivalent to a one-sided 97.5% CI) for the treatment difference (collagenase - surgery) at 1-year post-treatment, assuming a non-inferiority margin of six points and a standard deviation of 22 points. Assuming 20% attrition at the 1-year follow-up, the total target sample size is 710. The effective sample size of 568 is based on a (one-sided) independent samples *t* test of size 2.5%, neglecting information provided by informative baseline covariates (reference joint and baseline PEM score) and repeated measurements of the PEM.

The primary analysis will condition on these baseline covariates and will model PEM scores at all post-treatment time points using a covariance pattern model. Assuming the model assumptions are at least approximately satisfied, this approach would be expected to deliver greater statistical power at a given sample size, than the unconditional analysis on which the chosen sample size is based.

##### Recruitment {15}

Strategies for achieving adequate participant recruitment will include seeking advice from our patient focus group and completion of recruitment evaluation interviews with site teams.

Trial training and discussions in relation to key study elements will be implemented through face-to-face meetings with the PI’s at BSSH conferences and routine site investigator meetings.

Research teams will be provided with training at a site initiation visit and a trial manual will be provided to ensure adherence to trial processes. Support and guidance will be provided to staff when required (e.g. when new staff join or replace existing site staff) with clinical guidance from the Chief Investigator when necessary.

#### Assignment of interventions: allocation

##### Sequence generation {16a}

Eligible, consenting participants will be randomised 1:1 to either collagenase injection or limited fasciectomy. Block randomisation with randomly varying block sizes will be used, stratified by the reference joint type (MCP or PIP).

As a result of the withdrawal of marketing authorisation for the study intervention (collagenase), resulting in limited availability within the UK, the randomisation sequence was amended, with effect from the 21st of January 2020, to include stratification by the centre.

In both SWATs, participants will be randomised in a 1:1 ratio, stratified by DISC trial allocation.

##### Concealment mechanism and Implementation {16b} {16c}

The trial statistician, independent of the participating NHS Trust sites, will generate the allocation sequence for the main trial. Randomisation will be completed using a secure, central online randomisation service hosted by Sealed Envelope Ltd.

Treatment will be allocated on an individual named participant basis, and the participant will receive their allocated treatment as soon as possible after randomisation. Following randomisation, a letter will be sent to the GP for filing in the participant’s records.

The trial statistician will also generate the allocation sequence for the retention SWATs and will provide the randomised allocations to the central coordinating team for implementation.

#### Assignment of interventions: Blinding

##### Who will be blinded and procedure for unblinding if needed {17a/17b}

Neither the study design nor the interventions allow for the masking of clinicians or participants; therefore, an unblinding procedure is not required for this study.

The interventions used in the nested sub-studies are deemed to be low risk, and therefore, unblinding for these components is not required.

Due to the way in which data will be collected will also not be possible to blind the statistician to trial allocation for the analysis. All analyses will be pre-specified in a statistical analysis plan, and any changes made to the data set prior to analysis will be documented appropriately.

#### Data collection and management

##### Plans for assessment and collection of outcomes {18a}

Case report forms (CRFs) will record all required information with separate CRFs collecting clinical and patient-reported information. Copies of CRFs used in the trial are available on request.

##### Plans to promote participant retention and complete follow-up {18b}

Participants will receive £40 following completion of each of the 1-year and 2-year participant outcome questionnaires. This strategy has been found to have an effect on improving participant retention and questionnaire response rates [20, 21].

Participants will also be sent a study newsletter 4 weeks before the 1-year time point to maintain engagement with the trial and to encourage attendance at the 1-year study visit. This will be accompanied by a cover letter from the study Chief Investigator to thank them for their continued contribution to the study.

The coordinating centre at the University of York will liaise with trial sites to ensure that visits for the 1-year primary outcome time point are arranged accordingly. Where a visit cannot be arranged within 4 weeks of the visit due date, a postal questionnaire will be sent to the participant. If there is still no response after a further 4 weeks, the participant will be telephoned to collect their data.

A SWAT testing a thank you card is also embedded within the DISC trial. Participants will be individually randomised to either receive a thank you card at months 9 months post-treatment, or to receive a no-thank-you card at this time point.

##### Data management and confidentiality {19} {27}

All data will be stored and handled in accordance with data protection principles.

Data will be entered, checked and validated using an automated, electronic system (Teleform) as licensed for use at the UKCRC-registered University of York Trials Unit (YTU). A data management plan will document details of the data processing.

All participant data will be identified by a coded number to maintain participant confidentiality.

Paper documents will be stored in locked cabinets in restricted access areas either at the University of York or at an alternative secure off-site facility. Electronic records will be stored on a password-protected server.

Photographs of participant’s hands will be anonymised prior to electronic transfer by sites to YTU. Images will be stored in an encrypted and password-protected drive and will be transferred via secure and encrypted systems to the University Hospitals of Leicester NHS Trust for processing. Participant details required to facilitate contact and arrangement of the qualitative sub-study will be provided to colleagues at the University of Nottingham and University Hospitals of Leicester NHS Trust via secure and encrypted systems.

Participants’ data may be reviewed by authorised persons to verify that the study is being carried out correctly; all of whom will have a duty of confidentiality. Trial participants will give permission for this at the time of consent. All names and other identifying information will be removed before the data are analysed and the results presented and published.

Essential trial documentation relating to the conduct of the trial and the data produced will be kept within the Trial Master File and Investigator Site Files. This documentation will be is retained in accordance with guidelines on Good Research Practice and UK Law. Paper data will be disposed of securely and electronic data will be anonymised.

##### Plans for collection, laboratory evaluation and storage of biological specimens for genetic or molecular analysis in this trial/future use {33}

No plans are required for collection, evaluation or storage biological specimens given; these are not collected within the DISC trial.

Compliance with randomised treatments will be reported, and an instrumental variable estimator (assuming random allocation is a valid instrument) will estimate the Complier Average Causal Effect (i.e. the average causal effect of collagenase compared to surgery among the “complier” principal stratum). The primary analysis assumes missing outcome data are missing at random (MAR) conditional on the baseline covariates and non-missing outcomes included in the model. Multiple imputations will be used to make the MAR assumption more plausible, via imputation of missing outcomes conditional on additional informative pre- and post-randomisation variables. A mean score approach will also be used to explore the sensitivity of the results of the primary analysis to various systematic departures from MAR [24].

Continuous secondary outcomes (URAM, MHQ, SANE and active/passive range of movement) will be analysed using similar covariance pattern models as used for the primary analysis. Categorical outcomes (recurrence, complications, further procedures and overall hand assessment) will be analysed by appropriate logistic regression models. Time elapsed between the initial treatment of the reference digit and receipt of further treatment to the reference digit will be analysed using a Cox proportional hazards regression model. Secondary analyses will focus primarily on interval estimation, as opposed to hypothesis testing, under either a non-inferiority or superiority testing framework.

#### Economic analysis

The economic evaluation will estimate the relative cost-effectiveness of collagenase compared with surgical treatment.

The short-term effect of collagenase and limited fasciectomy treatments will be assessed using a within-trial cost-utility analysis (CUA) with a 1-year time horizon. If collagenase is cost-effective in the short term, we will extrapolate cost-effectiveness estimates over time. Hence, the primary analysis will be a recurrence model based on DISC evidence. The outcomes of the model will be used to estimate the incremental cost-effectiveness ratio (ICER) of the two treatment options.

Needle fasciotomy is also used as standard care in the NHS for the treatment of Dupuytren’s disease. Since the start of the trial, a number of literature review searches have been conducted to identify publications relevant in this area. Based on the evidence identified through this review, we will conduct a scenario analysis to assess the impact of incorporating needle fasciotomy into the comparison. Finally, a threshold analysis will be used to determine the threshold value of the effectiveness of limited fasciotomy and percutaneous needle fasciotomy, leading to these interventions being cost-effective. The analysis will be consistent with the NICE Guide to the Methods of Technological Appraisal [25] and Decision Modelling for Health Economic Evaluation [26].

Data on resource use and health-related quality-of-life will be collected alongside the trial. Intervention costs will be estimated according to injection and manipulation resource use. Surgical costs will be based on theatre and staff time, consumables and devices, and nights in the hospital after the procedure. The impact of the two interventions in the following costs will be collected using patients’ questionnaires and hospital forms (i.e. outpatient visits, hospital readmissions, A&E visits, general practice, and community and personal health services). The primary analysis will follow an NHS and Personal Social Services (PSS) perspective consistent with that used by the NICE. A secondary analysis will also consider productivity costs and private expenditures.

Health outcomes will be expressed in terms of quality-adjusted life year (QALY) using the EQ-5D-5L (i.e. collected at baseline; 2 and 6 weeks; 3, 6, 12 and 24 months). The EQ-5D-5L health states will be valued following the NICE position statement [27], and utility scores will be converted into QALYs using the area under the curve analysis [28].

Costs and QALY data will be synthesised to generate an incremental cost-effectiveness ratio (ICER). The probability that each intervention is cost-effective will be reported at the cost-effectiveness thresholds of £20,0000 to £30,000/QALY [25] and also £13,000/QALY [29, 30]. Regression methods will be used to allow for differences in prognostic variables. The pattern of missing data will be analysed and handled by multiple imputations if deemed appropriate [31]. Sensitivity analyses were conducted to test the robustness of the results.

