### Trial design {8}

The DISC trial is a two-arm, pragmatic, non-inferiority, randomised controlled trial investigating whether collagenase injection is not inferior to limited fasciectomy in the correction of Dupuytren’s contracture of the hand. The trial includes an economic evaluation, a qualitative sub-study, a photography sub-study and two nested studies within a trial of retention strategies.

**Table 1 Tab1:** DISC trial objectives

Objective	
1	To investigate whether collagenase injection is not inferior to limited fasciectomy in the *(impact of)* correction of Dupuytren’s contracture of the hand at 1 year^a^.
2	To investigate whether the *(impact of)* correction achieved after collagenase injection or surgical correction is maintained at 1 and 2 years^a^.
3	To investigate the cost-effectiveness of collagenase injections compared to limited fasciectomy at 1 and 2 years after treatment (from the NHS and Personal Social Services perspectives).
4	To investigate if the remote measurement of active extension and flexion using photographs is as good as goniometric measurements in a clinic to determine recurrence (photography sub-study).
5	To explore patient’s experiences and preferences of the different treatments (qualitative sub-study).

^a^*In terms of patient-reported hand pain and functionality as assessed by the PEM, as further detailed in the “Outcomes” section*

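### The economic section makes its own primary model, and any analysis beyond 1 year, appear to depend on a result favourable to collagenase, so the 2-year cost-effectiveness objective has no assured analysis

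*Protocol article*

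**What the plan says.** Objective 3 in Table 1 (Trial design {8}) is "To investigate the cost-effectiveness of collagenase injections compared to limited fasciectomy at 1 and 2 years after treatment", with no condition attached to either time point.

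The Economic analysis section sets out three steps in succession. The short-term effect is addressed by a "within-trial cost-utility analysis (CUA) with a 1-year time horizon". Next comes "If collagenase is cost-effective in the short term, we will extrapolate cost-effectiveness estimates over time". Then: "Hence, the primary analysis will be a recurrence model based on DISC evidence". The model's output is to give the incremental cost-effectiveness ratio (ICER).

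The same section lists the EQ-5D-5L data behind the QALYs as "collected at baseline; 2 and 6 weeks; 3, 6, 12 and 24 months". Table 2 (Outcomes {12}) schedules both EQ-5D-5L and resource use at 2 years. The probability of cost-effectiveness is to be reported at "cost-effectiveness thresholds of £20,0000 to £30,000/QALY [25] and also £13,000/QALY".

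**The concern.** A trial that describes itself as a cost-effectiveness trial should fix in advance which economic analysis is primary and ensure that it will be done. Here the word *Hence* derives the primary analysis from a sentence that begins with *If*. Taken at face value, the condition lets the direction of the 1-year result decide whether the longer-term question is asked at all.

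Two things are at stake. First, the headline economic analysis might not exist if the 1-year result goes against collagenase. Second, the 2-year half of objective 3 might go unanswered although its data have been collected. The second year also matters for substance: the trial gives priority to recurrence, and recurrence and re-treatment costs build up over time.

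**Working it through.** The documents give no cost or QALY differences and no standard deviations for them, so there is no economic figure to reproduce. The check is a comparison of the passages, with one small illustration on the thresholds.

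**Step 1. What is promised and what is provided.**

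| Item | 1 year | 2 years |
|---|---|---|
| Objective 3 (Table 1) | promised | promised |
| EQ-5D-5L and resource use (Table 2) | collected | collected |
| Named within-trial analysis (Economic analysis) | yes, unconditional | none named |
| Route beyond 1 year (Economic analysis) | not applicable | extrapolation, if collagenase is cost-effective in the short term |

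The 1-year half of the objective is covered. For the second year the data are there, but the only analysis described is the conditional one.

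**Step 2. The two readings of the conditional sentence and the one after it.**

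- *The condition governs.* If the 1-year result is favourable, the 1-year analysis and the recurrence model are both done. If it is unfavourable, only the 1-year analysis is done: the designated primary analysis is missing and nothing is reported at 2 years.
- *The model is unconditional.* It is run either way, and the conditional sentence is then wrong and should go. Even so, no 2-year within-trial analysis is named, and the section does not say that the model will report at 2 years.

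The first reading is the natural one because of *Hence*. Under neither reading does the section, as printed, assure the 2-year half of objective 3.

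**Step 3. Is the trigger defined?** The section does not say what counts as cost-effective in the short term. The thresholds it lists are for reporting probabilities, and none is named as the trigger. The choice can matter. Take incremental net benefit = saving − threshold × QALY loss, and *assume* that collagenase loses 0.02 QALY at 1 year. The savings below are also assumed.

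| Assumed saving | at £13,000 | at £20,000 | at £30,000 |
|---|---|---|---|
| £300 | 300 − 260 = +£40 | 300 − 400 = −£100 | 300 − 600 = −£300 |
| £400 | 400 − 260 = +£140 | 400 − 400 = £0 | 400 − 600 = −£200 |
| £500 | 500 − 260 = +£240 | 500 − 400 = +£100 | 500 − 600 = −£100 |

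With that QALY loss, any saving between 13,000 × 0.02 = £260 and 30,000 × 0.02 = £600 is favourable at the lowest threshold and unfavourable at the highest. If collagenase both saved money and gained QALYs, the choice of threshold would not matter. The table shows only that an undefined trigger can give different answers from the same data.

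**Step 4. The misprint.** The lower bound of the reporting range is printed as £20,0000. Read literally as £200,000, it would exceed the upper bound of £30,000, so £20,000 is evidently meant.

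**The case against.** The best case for the plan has four parts.

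- **The primary-analysis sentence carries no condition of its own.** Neighbouring text treats the modelling as settled work: the model will yield the ICER, a needle fasciotomy scenario will be run, and a threshold analysis will follow. This stands. It is why the section is called self-conflicting here, and not plainly gated.
- **The 1-year horizon is stated only for the short-term effect.** A reader might infer that it is incompatible with the 2-year objective. It is not: it serves the 1-year half, and 24-month EQ-5D-5L is listed among the QALY inputs. A 2-year within-trial analysis is not excluded. It is simply not named, and the only stated route past 1 year is conditional.
- **A staged design could be sensible.** Background and rationale {6a} cites observational data suggesting more recurrence after collagenase at 3 years. Extrapolation would then tend to erode a short-term advantage, and modelling might seem pointless without one. But the protocol does not give this rationale. The same section says that robust comparative recurrence evidence is lacking, which is the stated reason for prioritising recurrence among the secondary outcomes. The condition would presume part of what the trial is meant to find out.
- **Detail may sit in a separate health-economics plan.** A decision rule could well be placed there. However, the article describes itself as the full protocol, and another plan would have to override the printed condition, not merely add to it.

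A reader might also infer that the long-term ICER will be biased towards collagenase, and try to put a figure on it. The documents do not support that. Any such figure needs an assumed true net benefit, an assumed trigger, and the assumption that the 1-year estimate feeds the model directly. If the trigger is a 1-year net-benefit estimate above zero, the average overstatement of that estimate when the model is run goes from 0.06 standard errors (true value +2 standard errors) to 2.37 (true value −2). The assumption determines the answer. The 1-year analysis is also planned regardless, so an unfavourable short-term result would not be hidden.

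**Conclusion.** The point holds as a faulty stated rule, not merely as missing detail. The section makes work beyond 1 year conditional on a result favourable to collagenase, ties its primary analysis to that condition, and leaves an unconditional 2-year objective without an unconditional analysis. The trigger has no defined threshold.

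Its extent is limited. It concerns one of the five objectives, chiefly the 2-year half, together with the identity of the economic primary analysis. The PEM comparison, the sample size and the power are unaffected. What the condition selects is whether the longer-term analysis is run; bias in its result is not shown, and no numerical size is claimed. That the primary model is conditional rests on the natural reading of *Hence*. The gap at 2 years does not depend on that reading. The threshold misprint needs correcting but carries little weight.

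**What to change.** In the Economic analysis section or the health-economics plan, before 1-year costs and QALYs are compared by arm:

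1. Delete the condition on short-term cost-effectiveness.
2. State that the within-trial cost-utility analysis will be reported at both 1 and 2 years.
3. State that the recurrence model will be run whatever the 1-year result.
4. Say which of these is the primary (base-case) economic analysis, and give its horizon.
5. Correct £20,0000 to £20,000.

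If the team wishes to keep a staged approach, it should fix the threshold and decision rule in advance, give the reason, and say how objective 3 will be answered at 2 years when the trigger is not met.

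The cost is small: wording, and a modest amount of extra analysis if the 1-year result is unfavourable. The 2-year data are already scheduled and the modelling is already foreseen. No new data or participants are needed.

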Initial clinical effectiveness studies comparing collagenase with placebo [5] and a systematic review in 2015 [9] indicated that collagenase is better than placebo, particularly for contractures affecting the MCP joint [5]. Observational data on recurrence of Dupuytren’s contracture (a change in extension deficit of 6° between 3 and 6 months, or 20° from 3 months to 1 year post-treatment [6, 10]) suggest that it is higher following collagenase treatment than surgery 3 years after treatment.

Current evidence of the cost-effectiveness of collagenase and surgical correction is based on small retrospective studies [9] and so conclusions are limited.

Despite the existing available evidence, there is no robust randomised controlled trial evidence available on the clinical and cost-effectiveness of collagenase compared with limited fasciectomy surgery. There is also currently no robust evidence on the comparative recurrence rates of Dupuytren’s contracture following treatment with collagenase compared with limited fasciectomy surgery. A sufficiently powered randomised controlled trial is required to fill this evidence gap. Therefore, the UK National Institute for Health and Care Excellence (NICE) commissioned a full-scale RCT to provide a definitive answer on the effectiveness of these treatment options.

Overall, collagenase injections would have to not be inferior to limited fasciectomy surgery to permit recommendation for general use. The Dupuytren’s Interventions Surgery vs Collagenase (DISC) trial was designed as a pragmatic multi-centre, randomised controlled, non-inferiority, cost-effectiveness trial comparing injections of collagenase into the cord to surgical correction in the treatment of moderate Dupuytren’s contracture in adult patients.

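### The 2-year half of the cost-effectiveness objective has no assured analysis, because work beyond 1 year is made conditional on a favourable 1-year result for collagenase

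*Protocol article*

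**What the plan says.** Table 1 of the protocol article (Trial design) sets Objective 3 without any condition: "To investigate the cost-effectiveness of collagenase injections compared to limited fasciectomy at 1 and 2 years after treatment".

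The Economic analysis section then describes how this is to be done. The short-term effect is to be "assessed using a within-trial cost-utility analysis (CUA) with a 1-year time horizon". The text continues: "If collagenase is cost-effective in the short term, we will extrapolate cost-effectiveness estimates over time. Hence, the primary analysis will be a recurrence model", and this model is to rest on the trial's own evidence. The model's output is to supply an ICER for the two treatments. No horizon is given for the model.

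The same section says that QALYs come from EQ-5D-5L "collected at baseline; 2 and 6 weeks; 3, 6, 12 and 24 months", by area under the curve, and that costs and QALYs are combined into an ICER. Neither statement carries a condition or a horizon. Table 2 schedules both EQ-5D-5L and resource use at 2 years.

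**The concern.** An objective fixed in advance should have an analysis that is carried out whatever the data show. Here the step beyond 1 year, and apparently the analysis named as primary, are reached only if the first result goes one way. The rule is also one-sided. An early result in favour of collagenase is examined over a longer period, but an early result against it is not.

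Stopping after an unfavourable first year is harmless only if a longer horizon could not improve the case for collagenase. That depends largely on how recurrence compares between the arms. The Background reports observational data suggesting more recurrence after collagenase at 3 years, but also says: "There is also currently no robust evidence on the comparative recurrence rates". Recurrence is one of the prioritised secondary questions of the trial, so the stopping rule leans on an answer that the trial is meant to provide.

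At stake is the 2-year part of one stated objective, and whether a reader can be sure that the primary economic analysis will be reported.

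**Working it through.** The plan gives no figure on this point to reproduce. The check is to follow the text through both possible outcomes.

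**What is fixed, and with what horizon**

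| Element | Source | Horizon | Condition |
|---|---|---|---|
| Objective 3 | Table 1 | 1 and 2 years | none |
| Within-trial cost-utility analysis | Economic analysis | 1 year | none |
| Extrapolation | Economic analysis | not stated | collagenase cost-effective at 1 year |
| Recurrence model, named primary | Economic analysis | not stated | follows from the conditional sentence through the word *hence* |
| QALYs by area under the curve, and ICER | Economic analysis | not stated; 24-month EQ-5D-5L listed | none |
| EQ-5D-5L and resource use | Table 2 | collected to 2 years | none |

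**Branch A: collagenase is cost-effective at 1 year.** The within-trial analysis answers the 1-year half of Objective 3. Extrapolation and the recurrence model follow.

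**Branch B: collagenase is not cost-effective at 1 year.** The within-trial analysis again answers the 1-year half. The condition for extrapolation fails and, on the natural reading, the recurrence model is not triggered. No sentence specifies a within-trial analysis at 2 years. The 2-year half of Objective 3 therefore has input data but no analysis assigned to it.

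**Could the missing 2-year result matter?** This can only be illustrated, because the article gives no expected costs or QALYs. Assume that collagenase costs £300 more and gains 0.010 QALY in year 1, and take a threshold of £20,000 per QALY, the lower end of the range in the article.

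- ICER at 1 year = 300 / 0.010 = £30,000.
- Net benefit at 1 year = 20,000 × 0.010 − 300 = −£100, so collagenase is not cost-effective and Branch B applies.

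Now let the year-2 QALY difference vary, with no further cost difference and no discounting:

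| Year-2 QALY difference | 2-year total | Net benefit at £20,000 |
|---|---|---|
| +0.010 | 0.020 | 400 − 300 = +£100 (ICER 300 / 0.020 = £15,000) |
| +0.005 | 0.015 | 300 − 300 = £0 |
| 0 | 0.010 | 200 − 300 = −£100 |
| −0.010 | 0 | 0 − 300 = −£300 |

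The conclusion reverses only if collagenase gains more than 100 / 20,000 = 0.005 QALY in year 2. If it gains less, or loses ground, the 1-year conclusion stands. The example shows that a reversal is possible under these assumptions. It does not show that one is likely.

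**The case against.** The strongest reply is that the text can be read more kindly. The condition grammatically governs only the extrapolation. The sentence naming the recurrence model as primary is itself in the plain future tense, and so is the later sentence giving the primary analysis an NHS and Personal Social Services perspective. The needle fasciotomy scenario and the threshold analysis are also promised without condition. On this reading the model always goes ahead. This has some force, and it is why the model's dependence on the condition is put here as the natural reading rather than as certain. It does not remove the problem: *hence* ties the model to the conditional sentence, and a reader cannot tell which is meant.

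Three stronger claims are tempting, and the article does not support them.

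- *The whole of Objective 3 may go unanswered.* It will not: the within-trial analysis at 1 year is unconditional.
- *The 2-year data are unused.* The 24-month EQ-5D-5L is listed among the QALY inputs, so a 2-year within-trial estimate is arguably implied. What is missing is a sentence that commits to it.
- *The trigger is defective because no single threshold is attached to it.* That is detail which an article may leave to a fuller plan.

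There is also a rationale for working in sequence. If recurrence is higher after collagenase, as the observational data suggest, the main worry is that an early advantage erodes, and that is examined in Branch A. The same data run against the year-2 gain needed for a reversal in the example. Both points lower the likely impact, but neither supplies the 2-year analysis that the objective promises.

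Finally, one might call this detail for an analysis plan. But the article states a rule, and that rule does not fit its own objective; it also describes itself as the full protocol.

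**Conclusion.** The concern holds in a limited form. Objective 3 promises results at 1 and 2 years, while the only economic analysis with a stated horizon ends at 1 year and the step beyond it depends on a favourable result for collagenase. After an unfavourable 1-year result, the 2-year half of the objective has no assured analysis.

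This conclusion rests on the wording alone and on no numerical assumption. Its extension to the recurrence model rests on reading *hence* as carrying the condition forward. The effect on the trial's economic conclusion cannot be sized from the article. The matter is confined to the economic evaluation: the PEM comparison, the sample size and data collection are not affected. It should be corrected, because the objective is explicit and the correction is cheap.

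**What to change.** In the Economic analysis section:

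1. Delete the conditional clause that opens "If collagenase is cost-effective in the short term, we will extrapolate cost-effectiveness estimates over time".
2. State that the recurrence model, already named as the primary economic analysis, is run whatever the 1-year result.
3. Replace the single horizon in "within-trial cost-utility analysis (CUA) with a 1-year time horizon" with a statement that the within-trial analysis is done at both 1 and 2 years, using the EQ-5D-5L and resource-use data already scheduled.

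No extra data collection is needed. The cost is a short wording change and analyst time. The downside is that the longer-horizon model has to be built even if the 1-year result is unfavourable to collagenase.
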